### Sample size and power

The primary outcome is change in percent overweight. Our estimated sample size was informed by the results of Foster et al. [18] who observed a mean decrease of 4.3 % in percentage overweight (SE = 1.1) in a YMCA-based pediatric obesity intervention over 6 months, and is based on the number of participants needed to detect an effect size of this magnitude with 80 % power assuming a one-sided test at alpha = 0.05. Given a final sample of 48 children and allowing for up to 20 % attrition, 60 participants will be recruited.

### Research setting

The YMCA of Southern Arizona (YMCA-SAZ) will play a significant role in the intervention. As a certified training center for the Y-USA Diabetes Prevention Program (YDPP), YMCA-SAZ administrators and staff have experience delivering the successful adult-focused YMCA Diabetes Prevention Program [8, 16]. Two sites will serve as study locations, at which intervention and assessment activities will be conducted. Both facilities are easily accessible by public transit. Membership demographics indicate substantial minority and underserved membership (~67 % Hispanic, 71 % eligible for free and reduced lunch). Both locations report high family memberships (in the hundreds). Standard amenities at all YMCA locations include full service childcare available to all members free of charge; community rooms and free Wi-Fi throughout; sports fields; cardio wellness centers with state-of-the-art strength and fitness equipment; group exercise facilities; a complete aquatics center; locker rooms; and a space dedicated to youth activities. In addition, both YMCA locations provide sports, recreation, and fitness activities tailored to families. YMCA family memberships will be provided free of charge to all participants for the duration of the study.

### Intervention development

The YMCA’s (adult-focused) Diabetes Prevention Program (YDPP) served as a guide for the development of the EPIC Kids program. The YDPP consists of a series of weekly lessons delivered by trained paraprofessionals at the YMCA over 4 months. Program goals are weight loss through healthy eating and increased physical activity; all activities provide opportunities to learn and practice lifestyle behaviors (e.g., identifying calorie-dense foods; beginning an exercise program). EPIC Kids was designed to retain the relevant, evidence-based features and structural elements of the successful adult-focused program, with two key adaptations related to content and delivery - content specific to youth and families and delivery of content using mobile devices - both designed to address and overcome potential barriers to implementation unique to youth and families.

#### Adaptation 1: Inclusion of content specific to youth and families

Congruent with the 2012 IOM Report [19] and guidelines set forth by an Expert Committee [20], target lifestyle behaviors in support of childhood obesity prevention are 1) make physical activity an integral and routine part of life; 2) eat a healthy diet (both quality and quantity); and 3) create food and physical activity environments to insure healthy options and behaviors are the routine, easy choice. Relevant content and activities drawn from the intervention literature [15, 21] were also integrated, including behavior change techniques associated with successful lifestyle behavior change (e.g., self-monitoring, reinforcement, goal-setting, coping strategies [22]). Curriculum was further enhanced with fun, interactive, and active content designed to provide children and their parents with opportunities to learn and to practice healthy lifestyle behaviors as a family. Parents will receive further support during the program with a series of “parent-only” discussions led by lifestyle coaches which will focus on promoting the use of proactive parenting practices such as role modeling healthy eating and activity, increasing availability/accessibility of healthy foods in the home, and offering frequent opportunities for children to be active [23].

#### Adaptation 2: Delivery of content using mobile devices

Anticipating a ‘hybrid’ intervention format with an alternating face-to-face/digital delivery, five out of twelve EPIC Kids sessions (40 %) were adapted for delivery through the study-provided tablet (Kindle Fire HDX7, Amazon). Best practices for mobile content design and delivery informed these adaptations, with a focus on the persuasive design elements associated with mobile health behavior change (e.g., engaging interface, relevant content, customized prompts for goal-setting, self-monitoring, and social support) [24] (Table 1).

**Table 1 Tab1:** Program goals, target behaviors, and behavior change techniques

Program goals	Target behaviors	Behavior change techniques
Make physical activity an integral and routine part of life	Encourage moderate-to-vigorous physical activity	Goal setting
	Manage screen time	Self-monitoring
Eat a healthy diet (both quality and quantity)	Promote nutrient dense foods with an emphasis on vegetables, legumes, and whole grains	Role modeling by others (especially parents and siblings)
	Limit energy-dense foods (especially high sugar, high fat snacks)	Social support
	Limit sugar-sweetened beverages	Problem solving
	Encourage adequate sleep	Feedback
Create food and activity environments to insure healthy options and behaviors are the routine, easy choice	Practice proactive food, physical activity, and media parenting	Positive self-talk
	Structure the home environment to support healthy choices	Mindfulness
	Plan ahead for meals (home and restaurants)	
	Make time for family meals, activities, and media	

### Formative research

Participatory methods were used to refine intervention content and delivery methods. Formative research partners included an external advisory board comprised of experts in diet, physical activity, youth development, diabetes, mobile technologies, and pediatric medicine; youth in the target age range (9- to 12-years-old); administrators and program staff at the YMCA of Southern Arizona and Y of the USA, and staff from The University of Arizona Cooperative Extension’s Garden Kitchen, a seed-to-table nutrition education program serving the City of South Tucson.

In September and October 2014, in-depth interviews were conducted with two YMCA administrators and four staff to explore factors influencing local adoption and delivery of EPIC Kids. Discussion topics included branding and licensing issues, and ongoing costs and resources associated with training, implementation, and evaluation. Interviews also explored resources needed to conduct the future large-scale study. Two researchers trained in qualitative procedures conducted the interviews, which were audio-recorded, transcribed, and coded to identify salient issues.

In October 2014 and March 2015, advisory board members reviewed intervention materials and assessed whether proposed topics and activities aligned with program goals, rated the potential of each topic and activity to influence obesogenic behaviors, and insured the proposed activities fostered skill acquisition and provided opportunities for further practice. Following advisory board review, content was revised and further refined by the research team during a series of user tests conducted February to April 2015 with five children aged 9- to 12-years-old recruited from the YMCA. Participants met with the research team during six, 1.5-hour sessions held every other week for twelve weeks. At each session, participants were asked to complete a series of scripted activities mimicking study engagement (e.g., goal-setting, food preparation and sampling, physical activities) and verbalize their reactions (i.e., “think aloud”) as they completed the activities. Participants also viewed sample content from weekly sessions and rated its acceptability, their comprehension, and enjoyment. Following recommended guidelines for qualitative data collection [25], session notes were summarized and coded by the research team to identify salient issues related to content and delivery. Findings from user tests were presented to study investigators and advisory board members, and following a second period of review by these stakeholders, final adjustments to the intervention were completed.

### Intervention structure and content

Each EPIC Kids session is 1.5 h in length; sessions are delivered weekly over 12 consecutive weeks. In addition to incorporating structural elements that promote fun, activity, and interactivity (e.g., hands on experiential learning, kid-led activities) among children, family members and coaches; content is focused on impacting modifiable diabetes risk factors including the home environment, parenting practices, diet quality, physical activity, screen media use, and sleep. Sessions are structured to foster skill building and provide repeated opportunities to practice healthy lifestyle behaviors. Each week has a similar format, beginning with family physical activity, and concluding with goal setting (Table 2); all activities incorporate evidence-based behavior change techniques and behavioral targets.

**Table 2 Tab2:** EPIC Kids intervention – weekly session format

Activity	Description	Rationale for activity
Drop-in physical activity	A “join-as-you-arrive” physical activity provides a preview of the PA activity of the week	Get kids and families moving instead of sitting upon arrival
Reflection	Groups families together to discuss previous week’s goal-setting to share challenges and successes; self-monitoring is discussed and incentivized	Foster between-family interactions, source of new ideas and inspiration for others, ‘accountability’
Food for thought	Live food demo and tasting opportunity focused on one of the three goal food groups: vegetables, legumes, whole grains	Prepare and taste healthy (and delicious) food
Family physical activity	These are fun physical activities the whole family can enjoy; minimal equipment required	Demonstrate activity can be fun, especially when the entire family gets involved
OR		
Kid physical activity and parenting discussion	Active and kids choices, and FUN; parents focus on a parenting energy balance topic during this moderated discussion	Demonstrate activity can be fun; Parents learn proactive parenting around media, food, and physical activity
Energy balance activity	Hands-on activities that provide families with foundational knowledge and opportunities to practice healthy lifestyle behaviors	Provide opportunities to skill-build and practice as a family
Goal-setting	Integral to behavior change, families work together to set goals around energy balance behaviors	Promote behavior change

### Content for hybrid program

Mobile-enabled content represents an enhancement compared to the traditional face-to-face intervention. Since this innovation is untested in our target population, we used previously established protocols [26] to insure appropriate tailoring for our intended audience – children and families. Our delivery approach is informed by the multimedia learning literature [27], which emphasizes individual differences in rates of learning and behavior change, and the importance of customized program delivery to fit participants’ preferences and abilities.

With input from our Advisory Board and instructional media design specialists, the team prepared intervention content for mobile delivery during October 2014 to May 2015. The infrastructure supporting delivery of mobile-enabled content was established *a priori* [28], thus, development activities focused on customization of the interface, and conversion of activities and interactive elements of EPIC Kids to a mobile-friendly format (see Figs. 2 and 3).

**Fig. 2 Fig2:**
[figure not shown]
EPIC Kids mobile screen shot – home page for week 3 activities

**Fig. 3 Fig3:**
[figure not shown]
EPIC Kids mobile screen shot – goal-setting and self-monitoring tool

### YMCA lifestyle coach training

Twelve YMCA Lifestyle Coaches – paraprofessionals hired by the YMCA to deliver the adult-focused YDPP – will be trained to deliver the EPIC Kids intervention to participating families. Selection of coaches will occur based on a positive recommendation by their YMCA supervisor, their own interest, and prior experience leading group education sessions. In preparation, coaches will complete 16 h of training led by university-based researchers and YMCA staff in July/August and November 2015. During these training sessions, coaches will have the opportunity to learn and practice all aspects of the EPIC Kids curriculum and master competencies necessary to encourage children and parents in lifestyle behavior change including fundamentals of healthy eating and exercise, proactive parenting practices, communication skills (including group facilitation), and organizational skills/time management [29]. Trainings will take place over several sessions; each session will provide a combination of classroom-style didactic lessons and mock group sessions where coaches lead activities while trainers and trainees act as participants. This type and amount of training has been shown effective in translating previous T2D prevention programs to community settings [16, 30].

### Intervention delivery

The intervention will be conducted over 12 weeks at two YMCA locations. Each location will engage up to thirty children and their parents. The program duration is informed by the length of the YMCA adult-focused Diabetes Prevention Program, as well as studies in adults [31, 32] and children [33] that suggest success in weight loss and behavior changes during the first 8 to 12 weeks of a program predict overall success. Each Y location will host up to three concurrent intervention groups (each comprised of no more than 10 families) led by two YMCA Lifestyle Coaches. Program activities will occur at times convenient to parents (typically, early evening or weekend). All activities will promote active learning (i.e., hands-on activities requiring movement, interaction) and provide opportunities to build and practice skills related to healthy eating and physical activity as a family. For participants in the hybrid intervention, content will consist of equivalent topics and activities as the face-to-face sessions, made accessible through the study website (Moodle Pty Ltd, Perth, Australia) and a study-provided mobile device (Kindle Fire HDX7, Amazon).

## Procedures

### Randomization

Two YMCA sites, [A] and [B], were randomly assigned to face-to-face versus hybrid intervention formats using a random number table. Based on alphabetical order and an even number selected, [A] was assigned to receive the face-to-face format and [B] was assigned the hybrid format.

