## Methods/Design

### Study design

The impact of the EPIC Kids intervention will be evaluated using a group-randomized, non-inferiority trial design with three data collection points: baseline, post-intervention (immediately post program completion at 12 weeks), and follow-up (24 weeks) (Fig. 1). The program will be tested with sixty, 9- to 12 year-old children and their parent(s) or primary caregiver(s) at two YMCA locations in Tucson, Arizona where families lack services and resources needed for T2D prevention. Randomization to delivery formats will occur by YMCA location to minimize between-group contacts. One site will conduct a face-to-face weekly YMCA lifestyle coach-led program, while the second site will host a program equivalent in duration, frequency, and content, also lead by YMCA coaches, but with 5 weeks (40 %) of content digitally delivered using study-provided mobile devices (Kindle Fire HDX7, Amazon). Thirty families will be recruited to participate in each intervention format; each family will be assigned to an intervention group led by two trained YMCA lifestyle coaches and consisting of up to 9 other families. Weekly sessions will occur over 1.5 h for 12 weeks.

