### Participants

Eligible participants are 9 to 12-years-old at study enrollment, have a BMI at or greater than the 85th percentile for age and sex, and have one or more of the following T2D risk factors: ethnic minority, first or second degree relative with T2D, conditions associated with insulin resistance or metabolic syndrome (including acanthosis nigricans, hypertension, dyslipidemia, polycystic ovarian disease, small for gestational age birth weight, maternal history of gestational diabetes [17]). Eligible children must also have a primary caregiver willing to participate in intervention sessions and activities (note: primary caregiver is an adult who most frequently prepares/obtains food, regulates media use, and provides physical activity opportunities for the child), be willing to use a study-provided mobile device throughout intervention, and speak and read English. Exclusion criteria are previously diagnosed Type 1 or Type 2 diabetes mellitus (this is not an exclusion criteria for the caregiver), psychiatric disturbances or mental illness, limitations preventing physical activity, or using medications known to cause weight loss or gain or affect appetite.

Participants will be recruited through pediatric and family medicine practices, the Southern Arizona YMCA membership, and the Tucson community (e.g., libraries, community centers, public health department, and local health fairs) using electronic announcements, flyers, posters, and word-of-mouth between May and August 2015, and between October 2015 and January 2016. Respondents will be invited to attend study information sessions held at participating YMCA locations where eligibility will be confirmed. Interested and eligible respondents will complete the informed consent process following University of Arizona Institutional Review Board-approved materials and methods and assigned a study location based on geographical proximity. Written consent will be obtained from parents; verbal assent will be obtained from youth and documented in writing by study staff. Families who are not yet YMCA members will be provided access to YMCA facilities free of charge for the duration of the study, with an opportunity to continue at a reduced rate after the study has concluded.

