### Statistical analysis

Outcome measures will be stratified by delivery format to assess whether the mobile technology-supported delivery of the intervention is as efficacious as the face-to-face format. Descriptive statistics for change in endpoints (mean, median, and standard deviation) between baseline and 12-week measurements will be computed separately for each program format (face-to-face or hybrid mobile technology-supported program). The statistical significance of the change at 12 weeks will be assessed using a paired t-test combining both formats. One-sided statistical tests will be used, as the interventions approaches are of interest only if they decrease the percentage overweight and lead to improvements in diabetes risk factors. Statistical significance is set at alpha = 0.05. Sample size constraints do not allow adequate statistical power to formally test for differences between the two formats. However, exploratory models using linear regression analysis will estimate the magnitude of the difference between the face-to-face and combined formats, adjusted for baseline levels and the potential correlation between the participants within a given YMCA (expected to be small). These parameter estimates will provide effect sizes to appropriately power a larger study comparing the two formats. Since this is a randomized comparison, confounding is not an issue as long as there is non-differential dropout between the two formats. Differential dropout between the two formats will be assessed using a Fisher’s Exact Test. Similar analyses will assess whether improvements are maintained after the intervention ends, by comparing the 24-week versus 12-week values. We acknowledge the potential for differential loss to follow-up and missing data. Baseline values of those who complete the study versus those who do not will be compared using two sample independent t tests and Fisher’s Exact Tests, as appropriate. Additional sensitivity analyses will use multiple imputation for missing values and an intent-to-treat analysis with baseline values carried forward.

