### Process evaluation and monitoring

The intervention has an a priori focus on scalability, replication, dissemination, and sustainability. Process evaluation and monitoring plans were created using the RE-AIM framework, a tool to assess the public health impact of health promotion interventions as described by Glasgow et al. [59]. RE-AIM consists of five dimensions: reach, efficacy, adoption, implementation, and maintenance. These data will be collected using a combination of qualitative and quantitative measures and will involve our community partners (YMCA administrators and staff), the YMCA Lifestyle Coaches (delivering the intervention), and study participants. (Table 3) We will assess reach, impact, and engagement of participants and their families, and the feasibility of delivering the program using the YMCA infrastructure to inform future adoption, implementation and maintenance of the program. Efficacy will be measured both as the main study outcomes (anthropometric, behavioral and physiological, feasibility and acceptability, and attrition) and as the fidelity of the delivery of the intervention (e.g. training of and observations of curriculum delivery from Lifestyle Coaches). Quality assurance will occur with structured training and certification of YMCA lifestyle coaches, who will have continued access to the training team to discuss issues related to content or group moderation. The research team will review weekly session logs from YMCA instructors for potential departure from the EPIC Kids model, and conduct repeated observations of intervention sessions. Study staff trained in qualitative procedures will conduct interviews with YMCA staff and administrators to assess needs and resources for the program and for the YMCA at the program mid-point (November 2015). Engagement with administrators through interviews and surveys will inform activities related to the local adoption, implementation, and maintenance of EPIC Kids such as participant recruitment, branding and licensing, anticipated costs and resources associated with coach training, and program implementation and evaluation beyond the life of the grant.

**Table 3 Tab3:** Process evaluation and monitoring plan

Conceptual category	Data collection instrument	Variables	When
Reach	Screening form	• Inquiries • Non-eligible • Recruitment/referral source	Screening

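### Format is foreseeable before families consent, so the plan is wrong that only differential dropout could confound the comparison of formats

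*Protocol article*

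**What the plan says.** The Randomization section of the protocol article gives the draw as a past event and states which site received which format: "Two YMCA sites, [A] and [B], were randomly assigned to face-to-face versus hybrid intervention formats using a random number table". The Study design section describes the same step as still ahead: "Randomization to delivery formats will occur by YMCA location to minimize between-group contacts". Neither gives a date.

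The Participants section puts recruitment in two windows, "between May and August 2015, and between October 2015 and January 2016". It describes entry in the future tense: "Respondents will be invited to attend study information sessions held at participating YMCA locations where eligibility will be confirmed". Eligible families then consent and are "assigned a study location based on geographical proximity". Every child in either format must also "be willing to use a study-provided mobile device throughout intervention", and every child needs a caregiver willing to take part in the sessions.

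The Process evaluation and monitoring section times its interviews with YMCA staff "at the program mid-point (November 2015".

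On bias between formats, the Statistical analysis section says: "Since this is a randomized comparison, confounding is not an issue as long as there is non-differential dropout between the two formats". It plans a Fisher's exact test for differential dropout. It also says that the exploratory format estimates will be used to power a larger study.

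**The concern.** Sites were randomised, not families. A family's format follows from its site, and its site from where it lives. Once the draw is known, nothing random is left at family level. A family that can foresee its format can decline because of it, and so never enters the trial.

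The statement on confounding names one threat, dropout that differs between formats. Selection at entry comes earlier and is not covered by that condition.

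At stake are aims that the article itself states. The third objective assesses feasibility, acceptance and retention under the two formats. The Study design section asks whether technology reduces burden and improves adherence in the hybrid condition, and it uses a non-inferiority label. Acceptance and adherence are the outcomes most likely to depend on whether a family likes the format.

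**Working it through.** 1. **Order of the draw and recruitment.** The Randomization section gives the draw's result, while the Participants section puts recruitment, eligibility and consent in the future. The natural reading is that the draw came first. The future tense in the Study design section means that tense alone does not prove it.

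2. **The second wave does not depend on tense.** The programme lasts 12 weeks, so its mid-point is at week 6. Assume that the November 2015 mid-point refers to the first groups.
   - Start, six weeks earlier: between 20 September and 19 October 2015.
   - End, six weeks later: between 13 December 2015 and 11 January 2016.
   - Second recruitment window: October 2015 to January 2016.

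   Families are therefore recruited while each site is already running its one fixed format.

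3. **From address to format.** Address determines the nearest site, and site determines format. Anyone who knows the draw can name a family's format from its address. The blinding described in the article covers staff who collect, enter and analyse data. It does not mention families, referrers or recruiting staff.

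4. **What the planned checks can see.** Take the plan's 30 families per format and its 20 % attrition: 30 × 0.20 = 6 dropouts in each. Fisher's test of 6/30 against 6/30 gives p = 1, however many families declined at either site before consent. The comparison of completers with non-completers, multiple imputation and baseline carried forward also use enrolled families only. Adjustment for baseline outcome levels does not adjust for preference for a format.

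5. **Site.** Two sites minus two format means leaves 2 − 2 = 0 degrees of freedom for variation between sites. A format difference cannot be separated from a site or neighbourhood difference, even with no selection at all.

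6. **Size.** The plan's own recruitment figure reproduces, 48 / (1 − 0.20) = 60, but says nothing about selection. The documents give neither the extent of selection nor the outcome difference of selected families. The following is an illustration on assumed values, not an estimate.
   - False difference = q × g, where q is the difference between sites in the share of a prognostic type of family, and g is that type's difference in mean change in percent overweight.
   - Assume q = 0.10 to 0.30 and g = 2 to 7 points. The result runs from 0.10 × 2 = 0.2 to 0.30 × 7 = 2.1 points.
   - Precision with 48 / 2 = 24 completers per format, ignoring clustering: SE = SD × √(2/24).
   - SD of change is assumed to be 7.6 to 12. The lower value is 1.1 × √48 = 7.6, if the cited SE came from 48 children. The upper value is what 48 children and 80 % one-sided power imply: 4.3 × √48 / (1.645 + 0.842) = 12.0.
   - SE = 2.2 to 3.5 points, and the 95 % half-width (1.96 × SE) = 4.3 to 6.8 points.

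   A bias of this order would lie inside the random error, so the data could not reveal it.

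7. **Direction.** If each site loses families who dislike its format, both formats look better accepted and better retained than they would among unselected families. In the difference these errors partly cancel, and cancel fully if equal. The sign of the net bias is unknown.

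**The case against.** The strongest reply is that the article never says families are told the format before consent. It lists site assignment after consent, and the date of the draw is not given. Recruitment scripts and consent wording belong to ethics-approved materials that are not shown, and an article often leaves these to the full protocol. This stands as far as it goes. A reader might infer that each family knows its format before consenting, but the text supports only that format can be foreseen.

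A reader might also infer that families can choose a format by attending the other site's session, or can be steered there. The text does not support this, because placement follows proximity and not the session attended. Declining is the route that remains open.

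The eligibility rules soften the problem. Every family must already accept sessions and a device, which amounts to accepting both formats in principle. That lowers the likely extent of selection but does not stop a family from declining.

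A further inference would be that the primary result is compromised. It is not biased by selection between formats: the primary analysis is a paired t-test on both formats combined, and the plan calls the format comparison exploratory and underpowered.

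Finally, format is confounded with site in any case, so concealment cannot rescue the comparison. That is true, but selection before consent is a separate source of bias, would persist with many sites per format, and can be reduced at little cost.

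None of these replies repairs the sentence on confounding. It is a positive statement in the article, and it is wrong whatever the unseen materials contain.

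**Conclusion.** The point holds in limited form. The sites appear to have been allocated before families are recruited, entry is through those sites with placement by proximity, and the second wave recruits while the formats are in use. Format is therefore foreseeable before consent, and enrolment may differ by format. Non-differential dropout does not make confounding a non-issue, because it says nothing about selection at entry or about the two sites.

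The between-format comparisons of acceptance, retention and adherence are affected. So are the non-inferiority label and the exploratory effect sizes intended for the larger study. The size cannot be derived from the documents; the 0.2 to 2.1 points above rest wholly on assumed inputs. The conclusion for the first wave assumes that the draw preceded recruitment. For the second wave it assumes only that the November 2015 mid-point means groups were then running.

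**What to change.** In the Participants and Randomization sections:
- Assign each family's site by the proximity rule at first contact, with no switching afterwards.
- Use one recruitment script and one consent form that describes both formats.
- Reveal the site's format only after eligibility, consent and baseline measures are complete.
- Count families who leave on learning their format as dropouts of that format, in the retention and adherence denominators.
- Report enrolment and baseline values by site and recruitment wave. The process evaluation already records inquiries and referral source at screening.

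In the Statistical analysis section, replace the sentence on confounding with wording such as: Differences between formats may reflect selection of families at entry and differences between the two sites, as well as differential dropout, and will be interpreted accordingly.

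The cost is a short amendment and changes to the script and consent form, with no extra participants, visits or staff. Reported retention may look slightly lower, because some families may leave on learning their format. Masking will be imperfect in the second wave, when formats may be known locally. The confounding of format with site remains.
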